#### Quantitative process measures

The theoretical model underpinning the therapy hypothesises that mood-related difficulties are maintained, at least in part, by individuals responding impulsively to intense mood states, and some of these responses further affecting mood as well as contributing to difficulties in everyday life. In order to test this hypothesis in a future, larger trial we plan to use the following self-report measures, which are included in the current study, to assess the acceptability of doing so: Positive and Negative Urgency Scales (PU & NU [45]),; Behavioural Activation in Depression Scale–Short Form (BADS-SF [46]).

As another means of assessing the process of change within therapy as part of a large, future trial, we plan to measure mood and activity repeatedly to allow us to look at the inter-relationships between these. In the current study, we plan to gather information on the feasibility and acceptability of collecting these data, having initially tested this method within our case series. Participants will be invited to report on their current mood and activity 5 times per day for 10 days via a purpose-built web application (momentary assessment block). These momentary assessment blocks will take place on three occasions: for 10 days following the intake assessment, for 10 days at 14 weeks post randomisation and for 10 days following the 30-week follow-up point.

#### Additional measures

At the 30-week follow-up point, participants will complete a feedback questionnaire within which they will be asked to rate (on a scale from 1 to 4) their satisfaction with the therapy, how acceptable it was and the likelihood they would recommend it to a friend (for those in the intervention arm), and their overall satisfaction with the research element of the therapy (both arms), and also to give written comment on their answers to each questions and any general comments on the therapy or research. A brief feedback questionnaire will be sent to those exiting the study early, at the point they exit, if they have indicated they would be willing to complete this.

To monitor and evaluate intervention and study safety, an ‘Asking about adverse events’ form will be completed following the intake assessment (a researcher will check on participants’ wellbeing within a week of the intake assessment), and at the 14-, 30- and 52-week follow-up points. Members of the research team will also follow up with participants in relation to any potential adverse events mentioned in ad-hoc communications, therapy contacts or via HEQ completion.

Participants will be invited to rank outcome measures according to which they would most wish to experience change upon. Rankings will be conducted at baseline, and at the 30-week follow-up point.

Participants will be asked about their concordance with their prescribed psychiatric medication using the single, overall compliance question from the Brief Adherence Rating Scale (BARS [47]) at intake, 14 and 30 weeks.

#### Qualitative interview

At 30 weeks (patient participants) and at the end of the trial (therapists), there will be audio-recorded qualitative interviews of approximately 60 min conducted by one of the research team exploring experiences of the therapy. Fifteen participants in the intervention arm, purposively sampled to span diversity in terms of demographic characteristics and outcome in terms of therapy attendance, will be interviewed. All therapists who have delivered at least one therapy session as part of the study will be invited to be interviewed.

The interview will allow participants/therapists to describe their views in detail. The interview will be informed by the topic areas highlighted in process evaluation guidance [48], namely fidelity and quality of intervention implementation, mechanisms of change and impact of context. Specifically, it will ask about how participants/therapists found the therapy, any perceived effects of the therapy, aspects that were helpful/unhelpful, and views on the length and delivery format of the treatment and the feasibility/acceptability of both the intervention and the outcome measurement (for participants). It will also ask about experienced process of change, including questions on hypothesised mechanisms but also leaving space for these to arise inductively from reports, as well as participants’ experiences of the impact of the context in which they received the intervention (their personal/social context, and the healthcare context). The interviews will follow a topic guide, but with flexibility to adapt this based on the answers given.

Data collection forms will be available on request from the Chief Investigator following completion of the trial.

### Procedure

Informed consent will be taken prior to or at commencement of the eligibility assessment by a member of the study team; consent will be re-affirmed verbally prior to qualitative interviews. Following the initial eligibility assessment and completion of baseline measures, participants will be randomised to either STABILISE plus TAU, or TAU. Those allocated to the intervention arm will commence treatment approximately 2 weeks after being deemed eligible. Assessments at 14, 30 and 52 weeks will involve participants completing self-report measures either online or on paper, according to their preference, as well as speaking to a member of the research team (online, by telephone or in person) to complete the measures that require contemporaneous researcher involvement. A default procedure will be followed in cases where participants do not respond to requests to complete measures, with the procedure being tailored in accordance with individual patient preferences, as discussed following acceptance to the study. Figure 1 displays the measures completed at each time point.

**Fig. 1 Fig1:**
[figure not shown]
Schedule of enrolment, interventions, and assessments (following SPIRIT template)

## Data analysis

### Statistical analyses

Given the feasibility design, data analysis will focus on a descriptive analysis of the feasibility objectives of the study. We will report recruitment rates (average number of participants recruited per month) overall and by site. Retention and completion of outcome measures at follow-up timepoints will be reported as numbers and percentages, overall and by each treatment group. Participant characteristics at baseline will be reported descriptively for each treatment group, using mean (SD) for continuous variables, and percentages for categorical variables.

Outcome measures will be reported descriptively for each treatment group at baseline and at each post-randomisation follow-up, i.e. 14, 30 and 52 weeks. For 30- and 52-week follow-up data, the between group mean differences for continuous variables (intervention minus control group) will be reported with a 95% CI. The between group mean difference will be derived from a linear regression model, which will include treatment group as a fixed effect and will also adjust for study site and use of medication for BDs (factors used in the randomisation procedure). The feedback questionnaire will be reported descriptively for those items that relate to the STABILISE + TAU group only; the overall satisfaction item will be reported descriptively by treatment group and with a between group mean difference and 95% CI (using a linear regression model as for the clinical outcomes).

Given the feasibility nature of the trial, all participants will be analysed according to their randomised group irrespective of treatment actually received (intention to treat principle). Analyses will include observed data only; no imputation of missing outcome data will be performed. To explore potential mechanisms of missingness, we will report the mean (SD) for baseline PHQ-9 and GAD-7 for participants with and without completion of all four potential primary clinical outcome measures at 14 weeks, overall and by treatment group.

Serious adverse events (SAEs) will be reported as number of SAEs using the ‘as treated’ approach: participants in the STABILISE + TAU group will be classed as TAU only if they do not attend at least one therapy session. (It is assumed that participants allocated to TAU only will not be able to access therapy sessions.) SAEs will be reported numerically by ‘as treated’ group during the 52-week trial period, and as the number and percentage of individual participants experiencing one or more SAEs during the 52-week trial period. In addition, a risk difference and odds ratio for experiencing one or more SAEs during the 52-week trial period will be reported, with 95% CIs. Analyses will be performed using Stata v18 or later, by a statistician who is blinded to group allocation.

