**Methods:**

Patients will be randomised 1:1 to either Treatment as Usual (control arm) or Treatment as Usual plus STABILISE intervention (intervention arm). Follow up points will be at 14, 30 and 52 weeks post eligibility confirmation, with 30 weeks as the primary end point. We aim to recruit 60 individuals meeting diagnostic criteria for a Bipolar Spectrum Disorder, and reporting ongoing bipolar symptoms (low mood or mood instability) outside of a manic or severe depressive episode. Feasibility and acceptability will be examined through recruitment and retention rates, completion rates for the candidate primary outcome measures (PHQ9, ALS-SF, QoL.BD and BRQ) and feedback from participants on their experience of study participation and therapy. Proceeding to a definitive trial will be indicated if the following criteria are met: (i) trial participation is deemed, or can be made, sufficiently safe; (ii) recruitment rate indicates that larger-scale recruitment would be feasible (recruitment rate of at least two participants per month within at least one site, with mitigation plan if overall target sample size not met); (iii) for candidate primary outcome measure follow up data is available at 30 weeks from at least 75% of participants, or from between 55 and 74% with clear plan for improvement.

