Overall safety of intervention and trial procedures as determined by TSC and sponsor^a^	Cannot be made sufficiently safe for use in a definitive trial		Can be made sufficiently safe following modification		Sufficiently safe for use in a definitive trial	
Mean recruitment rate per site over 15 months	< 2 participants per month at both sites		< 2 participants per month at one site and target sample size not reached, with clear plan for improvement		≥ 2 participants at both sites OR < 2 participants at one site but overall target sample size reached^b^	
Outcome measure completion at 30-week follow-up point (completion of candidate primary outcome measure at primary end point)	< 55% of participants		Between ≥ 55 and < 75% of participants, with clear plan for improvement		≥ 75% of participants	
Level of completion of intervention (defined as attending at least 6 therapy sessions)^c^	< 50% of participants		50–89% of participants, with clear plan for improvement		≥ 90% of participants	

Red: Do not progress to the main trial (unless TSC agree exceptional circumstances and a mitigation plan is present); Amber: Progress if action plan to mitigate problems can be determined and agreed with the Trial Steering Committee (TSC); Green: Progress directly to the main trial

^a^Subsequent to reviewing information on adverse and serious adverse events arising during the trial

^b^To allow for a situation in which recruitment systems require a lead-in period at a site before becoming optimized, and this optimization period can then be accounted for in planning for a definitive trial

^c^Information will be collected on reasons for discontinuation to inform plan for enhancing retention in intervention and/or refinement of the estimand for a definitive trial [28]

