### Design

This feasibility study has a two-arm randomised parallel controlled trial design. Participants will be randomised on a 1:1 ratio to Treatment as Usual (TAU) only (control arm) or TAU plus STABILISE programme (intervention arm). Outcome measures will be completed at baseline and at three follow-up points: 14, 30 and 52 weeks post study entry. We have selected 30 weeks as the primary end point to allow this to be immediately following the intervention period. The study takes a mixed-method approach whereby evaluation of therapy acceptability and potential impact is explored both qualitatively and quantitatively.

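### The completer versus non-completer comparison is fixed at 14 weeks, so it captures only part of those missing from the 30-week estimates

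*Protocol article*

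**What the plan says.** All references are to the protocol article.

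- **The check.** Under Statistical analyses, the article looks into possible reasons for missing data by summarising two baseline scores, PHQ-9 and GAD-7. The groups it sets against each other are those "with and without completion of all four potential primary clinical outcome measures at 14 weeks, overall and by treatment group". No reason is given for choosing 14 weeks.
- **The primary end point.** Under Design: "We have selected 30 weeks as the primary end point". The Methods part of the abstract agrees: "with 30 weeks as the primary end point".
- **The progression criterion.** Table 1, under Objectives, applies its retention row to "Outcome measure completion at 30-week follow-up point", with red below 55%, green from 75%, and amber between.
- **The estimates.** Under Statistical analyses: "For 30- and 52-week follow-up data, the between group mean differences for continuous variables" are reported with confidence intervals. The 14-week outcomes are only described by group. Missing outcomes are not imputed.

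**The concern.** An exploration of missingness is useful when it describes the people absent from the estimates that will be reported. Here those estimates are at 30 and 52 weeks. The comparison is attached to the one follow-up visit that has neither a between-group estimate nor a progression criterion.

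A participant with all four measures at 14 weeks who is gone by 30 weeks counts as complete. A participant who misses a measure at 14 weeks but supplies all four at 30 weeks counts as incomplete, although present in the 30-week analysis.

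Therapy starts about 2 weeks after eligibility (Procedure) and may run for up to 30 weeks (Trial intervention). At week 14 roughly 14 − 2 = 12 weeks of therapy have passed, so loss during the later part of treatment is outside what this table can show. The team could find similar baseline scores at 14 weeks and carry that reassurance over to 30 weeks, both when reading these estimates and when planning the definitive trial.

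**Working it through.** **1. Time points side by side**

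| Item | Time point | Where stated |
|---|---|---|
| Baseline comparison by completion status | 14 weeks | Statistical analyses |
| Primary end point | 30 weeks | Abstract; Design |
| Completion criterion | 30 weeks | Table 1 |
| Between-group mean differences | 30 and 52 weeks | Statistical analyses |
| Completion numbers and percentages | every follow-up | Statistical analyses |

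Only the first row stands at 14 weeks alone. The 14- and 30-week groupings agree only if nobody changes completion status between the two visits.

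**2. The plan's own attrition figure**

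The Sample size section gives n = 60, 20% attrition and a precision of ± 12 percentage points. For 12/60, 95% intervals are:

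- Wald: 1.96 × √(0.2 × 0.8 / 60) = 0.101, or ± 10.1 points.
- Wilson: 11.8% to 31.8%, an upper arm of 11.8 points.
- Exact: 10.8% to 32.3%, an upper arm of 12.3 points.

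The stated 12 is reproduced as the wider arm of the Wilson or exact interval. The present point does not depend on it. What matters is that the section attaches no time point to the 20%.

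**3. Illustration of the size**

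Assumptions: the 20% applies at 30 weeks; drop-out is permanent; each person supplies all four measures or none; 5% to 15% are missing at 14 weeks. The article gives no 14-week figure, so this range is an assumption.

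Number missing at 30 weeks but classed as completers = 60 × d30 − 60 × d14.

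| Missing at 30 weeks | Missing at 14 weeks | Classed as completers |
|---|---|---|
| 20% (12) | 5% (3) | 9 of 12 (75%) |
| 20% (12) | 10% (6) | 6 of 12 (50%) |
| 20% (12) | 15% (9) | 3 of 12 (25%) |
| 25% (15) | 5% (3) | 12 of 15 (80%) |
| 25% (15) | 10% (6) | 9 of 15 (60%) |
| 25% (15) | 15% (9) | 6 of 15 (40%) |

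The 25% rows correspond to the green threshold of 75% completion. With a constant drop-out rate and 20% missing at 30 weeks, d14 = 1 − 0.80^(14/30) = 0.099, or 5.9 people. That leaves about 6.1 of the 12, roughly half, in the completer group.

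**4. How much a 30-week table could show**

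With 12 non-completers and 48 completers, the 95% half-width for a difference in baseline means is 2.002 × √(1/12 + 1/48) = 2.002 × 0.323 = 0.65 SD. By arm, with about 6 and 24, it is 2.048 × √(1/6 + 1/24) = 2.048 × 0.456 = 0.93 SD. The table would be at the right visit, but it could neither establish nor exclude informative drop-out.

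**The case against.** The strongest reply is that this is a descriptive feasibility trial. It is not powered for between-group differences and not designed to assess effectiveness (Objectives, Limitations). No progression criterion uses the comparison: the retention row is a completion percentage at 30 weeks and is unaffected. With about 12 non-completers the table would be imprecise at any visit. All of this stands and limits the weight of the point. It does not explain why 14 weeks was chosen.

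A reader might infer more than the article supports:

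- **That this is the only information on missingness.** It is not. Completion is reported at every follow-up by group. The Economic analyses section will present losses to follow-up and discuss the causes of missing outcomes. Table 1, note c, collects reasons for stopping the intervention. Additional measures describes a feedback questionnaire for willing early leavers. What is missing is narrower: a baseline comparison by completion status at 30 weeks.
- **That it describes the wrong people altogether.** Those lost for good by 14 weeks are also missing at 30 weeks. The groups overlap; the 14-week one is incomplete.
- **That everyone lost between weeks 14 and 30 is counted as complete.** Only those with all four measures at 14 weeks are. Someone with a partial set is already a non-completer.
- **That PHQ-9 and GAD-7 are the wrong baseline variables.** Completion is defined on all four candidate outcomes, and a predictor of missingness need not be a candidate outcome. Adding the other baselines is a preference.

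An analysis plan that is not shown might add a 30-week table. The article does not leave the visit open, however. It names 14 weeks, so this is a stated mismatch and not an omission.

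**Conclusion.** The point holds in a limited form. The one planned baseline comparison by completion status is set at 14 weeks, while the primary end point and completion criterion are at 30 weeks and the differences estimated from available data are at 30 and 52 weeks. It therefore captures only part of those missing from the 30-week estimates.

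The 9 to 3 of 12 misclassified is an illustration, not a figure from the plan. It rests on placing the undated 20% at 30 weeks, on an assumed 5% to 15% missing at 14 weeks, and on permanent drop-out. The last is not assured: the article has a procedure for following up non-response (Procedure), and it does not treat stopping therapy as withdrawal from the trial (Criteria for discontinuation). If nobody changes status between the visits, the number is zero.

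The consequence is modest. It concerns how far the 14-week table can inform the reading of the 30-week estimates and the design of the definitive trial. It does not alter any estimate or progression decision.

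**What to change.** In Statistical analyses, specify that baseline PHQ-9 and GAD-7 will be summarised by whether all four candidate outcomes were completed at 30 weeks, and again at 52 weeks, overall and by treatment group. The 14-week table can stay as an addition. Adding the baseline values of ALS, QoL.BD and BRQ is optional.

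The change needs one sentence and one or two further descriptive tables. It needs no new data, since the baseline and completion data are collected anyway. The tables should carry a note that, with about 12 non-completers, they are too imprecise to rule informative drop-out in or out.

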The intervention consists of up to 20 individual therapy sessions (plus up to 2 initial assessment sessions) of behavioural therapy, delivered up to 7 months (30 weeks). Therapy ends after 20 sessions or 7 months, whichever is sooner, and participants can choose to space sessions out over more than a week if they wish or to take a short break from therapy. Sessions are an hour long as default but with the option for participants to agree shorter or longer (up to 75 min) session duration if needed. This is followed by a period of consolidation whereby participants can opt to see the therapist up to 3 times up until 12 months after starting therapy. All sessions will be audio-recorded (where participants consent to this) to allow for supervision and the refinement of a therapy adherence and competence measure.

Therapy will be delivered by at least three therapists with an existing training in cognitive behavioural, behavioural or dialectical behavioural therapy and experience of working with people with mood disorders. Therapists new to delivering the intervention will receive a 3-day training programme and all therapists will receive supervision every 1–2 weeks from the therapy developer or a STABILISE senior therapist whilst delivering therapy.

Therapy will be delivered face-to-face, online or by phone according to participant preference and what is feasible; local NHS service protocols will be followed in terms of telephone and online platform use. Face-to-face therapy will by default be delivered in the treatment centre; however, in keeping with the ethos of the approach (patient-centred, flexible, contextual and experiential) therapy sessions may take place outside of the centre if the participant wishes and it is appropriate and safe to do so. This may include practising activities together (e.g. visiting a shop) or sessions within the person’s home. Participants will complete the Beck Depression Inventory (BDI) [38] and Altman Self-Rating Mania Scale (ASRM) [39] prior to each session and the scores used to inform their care, as well as forming part of the research data collected.

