### Adverse events

We will monitor and record both serious and non-serious adverse events. Adverse event reports will be solicited at follow-up points and monitored during all research contacts and through inspection of HEQ responses. An adverse event (AE) is defined by the HRA as any untoward occurrence or worsening of an unintended sign, symptoms or disease that occurs during participation, regardless of any relation to participation. In the STABILISE study, an adverse event will be recorded only when medical/clinical assessment or treatment is sought for a new or worsening sign, symptom or disease, unless the event appears to be a result of participation in the study. An adverse event will be classified as serious if it results in death, life threatening injury or condition, permanent impairment to a body structure, body function or the capacity of the individual to function in daily life, hospitalisation or extension of existing hospitalisation, foetal death or a congenital abnormality or birth defect.

Symptoms of bipolar disorder themselves are not defined as adverse events. However, deterioration in mental state that results in the person accessing emergency support will be classed as an adverse event.

Any AEs that researchers or therapists believe may be study related, may merit a classification of ‘severe’ (even if not technically meeting SAE criteria) or may constitute an SAE will be required to be reported to the site PI, Trial Manager and the CI within 24 h. Other AEs must be reported to the PI, Trial Manager and CI within 1 week. The reporting period for all events and reactions will be from intake assessment to completion of the 52 week follow-up point.

The only expected reactions to the therapy and/or trial procedures are distress or symptom exacerbation (including behaviours such as self-harm, suicidal behaviour or substance use which may be considered to be part of the symptom set that individual typically experiences or may be considered to be coping responses in the face of distress or symptom exacerbation).

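### SAEs are compared only as treated, with STABILISE-arm non-starters added to the TAU group, so the randomised safety comparison is lost and can be biased in either direction

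*Protocol article*

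**What the plan says.** The Statistical analyses section sets a general rule: "all participants will be analysed according to their randomised group irrespective of treatment actually received (intention to treat principle". The Economic analyses section also uses intention to treat.

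SAEs are the exception. They are grouped as treated: "participants in the STABILISE + TAU group will be classed as TAU only if they do not attend at least one therapy session". Movement the other way is ruled out by assumption: "It is assumed that participants allocated to TAU only will not be able to access therapy sessions". The counts follow this grouping ("SAEs will be reported numerically by ‘as treated’ group during the 52-week trial period"), and on the natural reading so do the percentages and the effect measures: "a risk difference and odds ratio for experiencing one or more SAEs during the 52-week trial period will be reported, with 95% CIs". No SAE summary by randomised group is stated.

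Three other places bear on the rule:

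- Procedure: "Those allocated to the intervention arm will commence treatment approximately 2 weeks after being deemed eligible".
- Adverse events: "The reporting period for all events and reactions will be from intake assessment to completion of the 52 week follow-up point".
- Trial intervention: up to 20 therapy sessions, "plus up to 2 initial assessment sessions". The SAE rule does not say whether attending an assessment session is enough to be classed as STABILISE.

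**The concern.** The SAE groups are defined by something that happens after randomisation and that the outcome can influence. There is a wait of about two weeks between eligibility and the start of therapy, and SAEs are already being recorded during it. Hospitalisation is an SAE under the protocol's definition. If a hospitalisation keeps a STABILISE-arm participant from ever attending, both the person and the event are moved to the comparator. Any later SAE in a non-starter, up to week 52, moves as well.

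The movement is one-way, and it changes both risks at once: the STABILISE group loses these people and the TAU group gains them. The resulting risk difference and odds ratio compare therapy starters with a mixture of the TAU arm and STABILISE-arm non-starters, which is not a randomised comparison. At stake is the only between-group SAE estimate that the protocol specifies, in a trial where Table 1 makes safety a progression criterion for the intervention and the trial procedures together.

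**Working it through.** The protocol gives no SAE rate, non-start rate or SAE precision figure, so there is no figure of its own to reproduce.

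**From the document.** 60 participants randomised 1:1, so about 30 per arm.

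**Assumed.** m = number of STABILISE-arm non-starters (1, 3 or 6); q = their SAE risk; r_s = SAE risk in starters; r_t = SAE risk in the TAU arm (10%).

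**Formulas for the expected risk difference (RD), STABILISE minus TAU.**

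- By randomised group: [(30 - m) × r_s + m × q] / 30 - r_t
- As treated: r_s - (30 × r_t + m × q) / (30 + m)

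When r_s = r_t = r these reduce to m(q - r)/30 and -m(q - r)/(30 + m). The two always have opposite signs unless q = r, when both are zero.

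**Example, r_s = r_t = 10%, m = 3, q = 50%.**

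- By randomised group: (2.7 + 1.5)/30 = 14.0% against 10.0%, RD +4.0 points, OR 1.47.
- As treated: 10.0% against (3.0 + 1.5)/33 = 13.6%, RD -3.6 points, OR 0.70.

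**Range.**

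| r_s | m | q | RD by randomised group (points) | RD as treated (points) |
|---|---|---|---|---|
| 10% | 3 | 0% | -1.0 | +0.9 |
| 10% | 3 | 10% | 0.0 | 0.0 |
| 10% | 1 | 50% | +1.3 | -1.3 |
| 10% | 3 | 50% | +4.0 | -3.6 |
| 10% | 6 | 50% | +8.0 | -6.7 |
| 15% | 3 | 50% | +8.5 | +1.4 |
| 15% | 3 | 67% | +10.2 | -0.2 |

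The last two rows show that where starters really do have a higher risk than TAU, the rule first shrinks the difference. With 3 non-starters the sign reverses only when q is about two thirds.

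**A null comparison by randomised group.** Suppose both randomised arms have an overall risk of 10% (3 expected cases each) and there are 3 non-starters.

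- q = 30%: (3 - 0.9)/27 = 7.8% against (3 + 0.9)/33 = 11.8%, RD -4.0 points, OR 0.63.
- q = 40%: (3 - 1.2)/27 = 6.7% against (3 + 1.2)/33 = 12.7%, RD -6.1 points, OR 0.49.

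In both cases the randomised comparison gives RD 0 and OR 1.

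**In counts.** Take 5/30 against 3/30 by randomised group: RD +6.7 points (Wald 95% CI -10.5 to 23.8), OR 1.80. If 3 people do not start and 2 of them have an SAE, the as-treated table reads 3/27 against 5/33: RD -4.0 points (95% CI -21.1 to 13.0), OR 0.70. In the opposite direction, 3/30 against 3/30 with no SAE among 3 non-starters becomes 3/27 against 3/33: RD +2.0 points, OR 1.25.

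**The case against.** Grouping safety data by treatment received is a common convention, and here it is openly pre-specified. A reader might infer from the rule that therapy will necessarily look safer than it is. The documents do not support that. It needs non-starters to carry a higher SAE risk than the others, and people may fail to start for unrelated reasons. The protocol also expects more adverse events to be reported in the intervention arm because of therapy contact (Adverse events section), which pushes the other way.

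Nor is all early harm moved: someone with an SAE during the wait who later attends one session stays in STABILISE. An SAE before any session cannot be caused by a session, although allocation or trial procedures could contribute.

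A reader might also infer that this table decides whether the trial progresses. It does not. Table 1 sets no threshold on a risk difference or odds ratio, and the Trial Steering Committee (TSC) and sponsor judge safety after reviewing adverse event information. The TSC carries the data monitoring functions (Trial governance), possible SAEs are reported individually within 24 hours, and particular attention goes to events that appear caused by research or therapy. Finally, the intervals at this sample size are too wide to support a safety conclusion under either grouping.

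All of this stands, and it limits the direction and the consequence. It does not justify a comparator that contains people randomised to the intervention as the only SAE comparison stated. Wide intervals do not help either: with few events, moving two cases is enough to change the sign of the reported estimate.

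**Conclusion.** The point holds as a should-fix. The SAE rule breaks the randomised comparison because classification depends on a post-randomisation event that an SAE can itself cause, and no analysis by randomised group stands beside it.

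The direction is conditional. If non-starters have a higher SAE risk than the others, which is plausible but not documented, therapy looks safer than it would by randomised group. With about 30 per arm and 3 to 6 non-starters the risk difference can change sign (for example +4.0 to -3.6, or +8.0 to -6.7 points). At equal risk there is no shift. At lower risk therapy looks slightly worse (-1.0 by randomised group, +0.9 as treated, with 3 non-starters at zero risk). Every rate behind these figures is an assumption. If everyone randomised to STABILISE attends a first session, the two groupings coincide.

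Whether an assessment session counts is an ambiguity to settle, not a separate error. The Trial intervention section lists those sessions as part of the intervention but apart from the 20 therapy sessions, so either reading is open.

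**What to change.** In the SAE paragraph of Statistical analyses:

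1. Make the between-group comparison by randomised group: number of SAEs, n (%) with at least one SAE, and the risk difference and odds ratio with 95% CIs.
2. Keep any exposure-based summary as a descriptive supplement. Show STABILISE-arm non-starters as a separate row, not added to TAU, and list STABILISE-arm SAEs as before or after the first session.
3. List SAEs between intake and randomisation separately. They are collected under the stated reporting period and bear on the safety of trial procedures, so they should not drop out of the report.
4. State whether attending an initial assessment session counts as attending a therapy session.

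The cost is a few sentences and a small amount of extra tabulation. Allocation, attendance and SAE records are already needed for the planned analyses, so no new data are required.
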